## Abstract

**Introduction:**

The National Emergency Laparotomy Audit (NELA) has reported that older patients (≥65 years) form a large percentage of emergency high-risk cases with increased postoperative morbidity and mortality. With the population continuing to age rapidly, it is clear that a greater understanding of the factors affecting surgical outcomes in older patients is required. Frailty is a relatively new concept taking into account a variety of factors that increase an individual’s vulnerability to increased dependency and death. Research has suggested that high frailty scores increase postoperative complications, length of stay and mortality but the majority of these studies have been carried out on elective patients. Knowledge of how frailty affects patients in an emergency setting would aid clinicians’ and patients’ decision-making process.

**Methods and analysis:**

This multicentre study will include consecutive adult patients aged 65 years and over undergoing emergency laparotomies over a 3-month period at 52 National Health Service hospitals across the UK. The primary outcome will be 90-day mortality. Secondary outcomes will include length of hospital stay, 30-day complications, change in level of independence and 30-day readmission. This study has been powered to detect a 10% change in mortality associated with frailty (n=500 patients).

**Ethics and dissemination:**

This study has been approved by the National Health Service Research Ethics Committee. It has been registered centrally with HRA for English sites, NRSPCC for Scottish sites and Health and Care Research Permissions Service for sites in Wales. Dissemination will be via international and national surgical and geriatric conferences. In addition, manuscripts will be prepared following the close of the project.

**Trial registration number:**

This study is also registered online at www.clinicaltrials.gov (registration number NCT02952430).

Strengths and limitations of this studyIt is a large-scale multisite study based in the UK.Data collated using the established and effective registrar led research networks.Frailty collated using the Clinical Frailty Scale, which is quick and simple to use.The Clinical Frailty Scale was the only frailty measure collected, a potential limitation.

## Background

The population is ageing. This has implications for healthcare provision, including surgery.^1 2^ The second report of The National Emergency Laparotomy Audit (NELA) in the UK found that over half of patients undergoing major emergency general surgical procedures were older adults (≥65 years) with the highest risk, longest length of stay and highest mortality. NELA had previously recommended input for older adults by elderly medicine specialists from findings in their first report, but this was only reported in 10% of all cases.^3^ Clinical decision-making in older patients can be difficult as they have the unique challenges of multimorbidity, polypharmacy and cognitive impairment which can occur separately or more commonly in combination. Several risk stratification methods exist to aid the surgical and anaesthetic team, but are limited as they are generally extrapolated from cohorts of much younger patients. A greater understanding of factors involved in surgical outcomes in older patients is therefore required.^4^

Frailty is defined as ‘a medical syndrome with multiple causes and contributors that is characterised by diminished strength, endurance and reduced physiological function that increases an individual’s vulnerability for developing increased dependency or death’.^5^ This definition is now commonplace in Geriatric medicine with frailty routinely assessed in every hospital in the UK with older peoples services.

Assessment of frailty in emergency surgery has been assessed in a limited number of studies. Of those, high frailty scores preoperatively correlate with increased postoperative complications, length of stay, 30-day and 90-day mortality and likelihood of institutionalisation.^6–8^ However, there is substantial methodological heterogeneity with few studies focusing solely on older patients, being prospective in design and including all surgical patients admitted to an acute surgical ward, rather only those undergoing emergency laparotomy. Knowledge of how frailty affects outcomes after emergency laparotomy will aid surgeons in decision-making in this complex group of patients but, most importantly, help to inform the consent process for patients and their families.

### Aims

To assess whether preoperative frailty correlates with outcomes in older surgical patients undergoing emergency laparotomy (Emergency Laparotomy and Frailty (ELF) study).

## Methods

### Study design

A multicentre observational study.

### Study setting

Hospitals in the UK that provide emergency general surgery have been invited to participate. Fifty-two hospitals have expressed interest in taking part in the audit. Research will be conducted using the established surgical and geriatric registrar-led research networks.^9 10^ The methodology for these networks is well described but in brief the networks provide a centrally coordinated research network that promoted and advertised the ELF study. Potential collaborators were invited to take part in data collection, via a standard expression of interest application. The central study team (described below) subsequently provided the ethical approval, protocol, central organisation and long-term delivery of the project. Support was provided by the North West Surgical Trials Centre (www.nwstc.org.uk).

### ELF steering committee

The steering committee comprises surgical trainees and consultant general surgeons, interested in outcomes for older people undergoing surgery. It is formed from two established research groups, the North West Research Collaborative (surgical trainees) and the Older Persons Surgical Outcomes Collaboration (OPSOC; surgeons and geriatricians). The steering committee is responsible for protocol design, data handling, analysis, dissemination of results and the preparation of manuscripts. The ELF steering committee is responsible for the use of data resulting from this project.

### Principal investigators

The principal investigators at each participating site are responsible for organising and leading the local ELF teams. They have submitted relevant documents to local Research and Development departments for approval and ensured that collaborators act in accordance with local clinical governance and guidelines. These local leads act as a link between the local ELF team and the ELF steering committee. They are the first point of contact for local collaborators and are responsible for the dissemination of information to local collaborators from the ELF steering committee.

### Inclusion criteria

Patients aged ≥65 years.Patients who undergo an expedited, urgent or emergency abdominal procedure on the gastrointestinal (GI) tract, including the following:

Open, laparoscopic or laparoscopic-assisted procedures.Procedures involving the stomach, small or large bowel, or rectum for conditions such as perforation, ischaemia, abdominal abscess, bleeding or obstruction.Washout/evacuation of intraperitoneal abdominal abscess (unless due to appendicitis or cholecystitis—excluded, see below).Washout/evacuation of intraperitoneal abdominal haematoma.Bowel resection/repair due to incarcerated umbilical, inguinal and femoral hernias (but not hernia repair without bowel resection/repair).

Bowel resection/repair due to obstructing/incarcerated incisional hernias provided the presentation and findings were acute.Laparotomy or laparoscopy with inoperable pathology (ie, peritoneal/hepatic metastases).Laparoscopic/open adhesiolysis.Return to theatre for repair of substantial dehiscence of major abdominal wound (ie, ‘burst abdomen’) or any major postoperative complication (including all operations meeting the above criteria occurring as a complication of previous non-GI surgery, specific examples available at www.nela.org.uk/criteria).

### Exclusion criteria

Frailty score not documented on preoperative admission clerking.Elective laparotomy/laparoscopy.Diagnostic laparoscopy/laparotomy where no further procedure is performed (N.B. if no procedure is performed because of inoperable pathology, then include).Appendicectomy +/-drainage of localised collection, unless the procedure is incidental to a non-elective procedure on the GI tract.Cholecystectomy +/-drainage of localised collection, unless the procedure is incidental to a non-elective procedure on the GI tract.(All surgery involving the appendix or gallbladder, including any surgery relating to complications such as abscess or bile leak is excluded. The only exception to this is if carried out as an incidental procedure to a more major procedure).Non-elective hernia repair without bowel resection.

Minor abdominal wall dehiscence unless causing bowel complication requiring resection.Vascular surgery.Caesarean section or obstetric laparotomies.Gynaecological laparotomy (however bowel resection performed as non-elective procedure for obstruction due to cancer would be included).Ruptured ectopic pregnancy, or pelvic abscesses due to pelvic inflammatory disease.Laparotomy/laparoscopy for pathology caused by blunt or penetrating trauma.All surgery relating to organ transplantation (including returns to theatre for any reason following transplant surgery).Surgery relating to sclerosing peritonitis.Surgery for removal of dialysis catheters.Laparotomy/laparoscopy for oesophageal pathology.Laparotomy/laparoscopy for pathology of the spleen, renal tract, kidneys, liver, gall bladder and biliary tree, pancreas or urinary tract.

### Patient identification and data collection

Patients will be screened for inclusion criteria by the local team. Data collection will be carried out using the case report form presented in the online supplementary appendix A. Hospital or National Health Service (NHS) number will not be entered into this form but will be kept separately with a key sheet.

10.1136/bmjopen-2017-017928.supp1Supplementary data

Basic demographics, comorbidities and polypharmacy data will be recorded. Comorbidities will be collected based on the Charlson Comorbidity Index, a validated measure of prognostic impact of multiple chronic illnesses.^11^ This will allow for standardisation of comparisons between any groups. Data will also be collected on baseline independence status, assessed by the number of times social services provide care (1–4 times), and living in a residential or nursing home, measured both predischarge and postdischarge.

Frailty will be measured using the Clinical Frailty Score (online supplementary appendix B). This has been validated for use to assess frailty in older patients who underwent general surgery and OPSOC has successfully applied this before in previous work in this area.^12^ The score ranks from 1 to 7 with a score of ≥5 being classed as frail.

Data will be collected on preoperative risk from scoring systems used commonly within emergency general surgery. This will include the P-POSSUM score^13^ and the American Society of Anaesthesiologist grade.^14^

Data will be collected on operative procedures performed. Information will be obtained from patient case notes on 30-day outcomes. This includes 30-day mortality and evidence of postoperative complications. These complications will be rated using the Clavien-Dindo classification (online supplementary appendix C). This will allow for complications to be rated and outcomes to be assessed together. Finally, information will be obtained from the patient notes regarding 90-day mortality.

A detailed summary of the study questions asked can be found in the online supplementary appendix A.

The timetable for data collection is given in table 1.

**Table 1 T1:** Timetable for data collection

Period	Date
Case identification period	20/03/2017 - 19/06/2017
Data collection completion date	19/09/2017
Validation completion date	30/09/2017

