### Validation

Data validation will be performed by local teams on 25% of data fields for 10% of cases. The validated fields will include key demographic and outcome data.

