### Statistical analysis and power calculation

Using OPSOC data, frailty exists in 28% of older patients admitted with emergency surgical conditions. Fifty-four per cent of the frail people who underwent surgery had died after 90 days. In order to detect a 10% difference in mortality rate at day 90 between frail and non-frail patients, a sample size of 480 is required, given an expected mortality proportion in those not frail of 0.075 and those frail of 0.175 (data from OPSOC), assuming an 80% power. We anticipate minimal patients who are lost to follow-up and to account for this, we will aim to recruit 500 patients.

Statistical support will be provided by OPSOC. Data will be analysed for correlation between frailty and postoperative outcomes, including 90-day mortality, complications and loss of independence.

Our primary analysis will be a logistic regression of 90-day mortality by frailty, adjusted for age (65–74, and >75 years old) and gender. We will carry out a secondary analysis of the primary outcome by including additional clinical mediators which are determined statistically important using a likelihood ratio test with a stepwise model fitting approach of nested regression models, and presented as a final multivariable model. All analyses will be presented as adjusted OR with associated 95% CIs and p values.

All other outcomes will be analysed as per the above analysis, but will be deemed secondary outcomes.

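### The only named source for 90-day mortality is the patient notes, and data collection closes 2 days after the last patient's day 90, so deaths after discharge may be missed

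*Protocol article*

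**What the plan says.** The abstract fixes the endpoint: "The primary outcome will be 90-day mortality". The section on patient identification and data collection gives its source: "Finally, information will be obtained from the patient notes regarding 90-day mortality". The 30-day outcomes have the same kind of source: "Information will be obtained from patient case notes on 30-day outcomes". No death register, GP contact or telephone follow-up is named for either. Hospital and NHS numbers stay off the case report form but are held separately with a key sheet.

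Table 1 gives the case identification period as "20/03/2017 - 19/06/2017", completion of data collection as 19/09/2017 and completion of validation as 30/09/2017.

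The power section says: "We anticipate minimal patients who are lost to follow-up". The Validation section says: "Data validation will be performed by local teams on 25% of data fields for 10% of cases"; the fields checked include outcome data, but no second source is named.

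**The concern.** The cohort is aged 65 and over and followed to day 90, and the plan expects many patients to have left hospital by then: it records living arrangements after discharge, intermediate care stay and readmission. A patient who goes home or to a care home and dies there weeks later may have no death entry in the notes being read. Nothing in the article separates a patient confirmed alive at day 90 from one whose record is silent. With a yes/no endpoint, a silent record can easily be entered as survival.

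Late recruits are most exposed, because a death outside hospital has little time to reach the notes before data collection closes. Two things are at stake: the absolute mortality figures, which the Background wants used in consent discussions, and the odds ratio for frailty if capture differs between frail and non-frail patients.

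**Working it through.** **Dates.** Day 0 is not defined in the article; I take it as the identification date.

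- Last patient: 19/06/2017 + 90 days = 17/09/2017. Data collection closes 2 days later, and validation ends 13 days later.
- First patient: 20/03/2017 + 90 days = 18/06/2017, which is 93 days before closure.
- Identified on 22/05/2017: day 90 is 20/08/2017, a margin of 30 days. From 22/05 to 19/06 is 29 of the 92 identification days, or 32%. About a third of patients have 30 days or less if accrual is even.

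**The plan's own figure.** The power section gives "expected mortality proportion in those not frail of 0.075 and those frail of 0.175" and states that "frailty exists in 28% of older patients admitted with emergency surgical conditions". Alpha is not stated; I assume 0.05 two-sided. With 80% power and unpooled variance:

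N = (1.960 + 0.842)² × [0.075 × 0.925/0.72 + 0.175 × 0.825/0.28] / 0.10² = 480.3

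This matches the stated 480, so the same formula is used below at the target of 500.

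**Expected deaths.** 500 × (0.72 × 0.075 + 0.28 × 0.175) = 27.0 + 24.5 = 51.5.

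**Effect of missed deaths.** The documents give no capture rate, so the missed shares are my assumptions, and each missed death is taken as recorded alive. Observed risk in each group = true risk × (1 − share missed). Power = Φ(difference/SE − 1.960), with SE² = p₀(1 − p₀)/360 + p₁(1 − p₁)/140.

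| Missed, non-frail / frail | Deaths missed | Difference (points) | Odds ratio | Power, N = 500 |
|---|---|---|---|---|
| 0% / 0% | 0 | 10.00 | 2.62 | 81.6% |
| 5% / 5% | 2.6 | 9.50 | 2.60 | 79.2% |
| 10% / 10% | 5.2 | 9.00 | 2.58 | 76.6% |
| 20% / 20% | 10.3 | 8.00 | 2.55 | 70.9% |
| 5% / 10% | 3.8 | 8.63 | 2.44 | 72.7% |
| 10% / 20% | 7.6 | 7.25 | 2.25 | 61.6% |
| 20% / 10% | 7.9 | 9.75 | 2.93 | 83.5% |

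Equal missing hardly touches the odds ratio but lowers the absolute risks, their difference and the power. Unequal missing biases the odds ratio downwards when more frail deaths are missed, and upwards in the reverse case.

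The power levels depend on the formula. A pooled-variance test gives 87.7%, 86.0% and 84.0% at 0%, 5% and 10% missed equally. The loss is real under either formula, but falling below 80% at these rates is specific to the formula that reproduces 480.

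**The case against.** The strongest reply is that the article does not say silent records count as survivors. The power section treats loss to follow-up as a category of its own and raises 480 to 500 for it, which suggests that unknown status is recognised. The case report form (appendix A) is not shown and may define how survival is confirmed, and the article does not limit the notes to those of the operating hospital. The plan also gathers some information after discharge. This stands: a reader might infer that deaths will be missed and coded as survival, but the documents support only that they may be.

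The timing is also milder than the 2-day figure suggests. That margin belongs to the last day's patients. With even accrual the average margin is about 47 days, and 12 of 92 identification days (13%) leave under two weeks. Validation adds 11 days after closure, but only for a tenth of cases.

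A reader might further infer that capture is worse in frail patients and that the odds ratio is therefore understated. The Background links frailty with institutionalisation, but nothing in the article links it with death ascertainment, and the reverse pattern would inflate the odds ratio.

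The reply does not remove the point. A source for the primary endpoint is stated, and as written it need not capture deaths outside hospital. That is a method the article fixes, not a detail it merely omits.

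**Conclusion.** The point holds as a risk of under-ascertainment, not as a demonstrated bias. The text directs sites to the patient notes for the primary endpoint and names no safeguard for discharged patients; the timetable sharpens this for late recruits.

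On assumed equal missing of 5% to 10%, about 3 to 5 of some 51 expected deaths are lost, the difference shrinks by 0.5 to 1.0 points, and power falls by 2.4 to 5.0 percentage points on the plan's own formula. The odds ratio changes materially only if missing is unequal, and the documents give neither the rate nor the direction. These figures rest on the plan's frailty prevalence and mortality proportions, on missed deaths being recorded as alive, and on identification being day 0. The sample size calculation itself is not in error on this point.

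**What to change.** In the data collection section, replace the notes as sole source. Local teams should use the existing key sheet to confirm vital status and date of death for every patient, on or after day 90, from a source that captures deaths outside hospital. That could be the NHS demographic record available in that nation or the GP practice, within the approvals held. Code a patient as alive at 90 days only with dated evidence on or after day 90; otherwise code unknown. Move the data collection and validation dates in Table 1 a few weeks later.

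The cost is one look-up per patient, about 10 per site (500/52), a field for source and date, and a slightly later data close. Sites lie in England, Scotland and Wales, so access to records will differ, and a minor approval amendment may be needed. No extra patients are required, and no identifiers need to enter the central database.

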### Primary outcome

90-day mortality

### Secondary outcomes

Length of hospital stay (measured in days)Postoperative complications (yes/no and Clavien-Dindo grade of complication)

Change in level of independenceLength of stay on high dependency unit and intensive care unit (measured in days)Intermediate care stay on discharge (yes/no and duration of stay measured in length of days)30-day mortality30-day readmission

### Quality assurance

The study has been registered (www.clinicaltrials.gov, registration number NCT02952430).

The quality of this study has been assessed by the following means:Steering group meetings: 03/10/2016 and 13/12/2016.
Review by OPSOC.Peer review by professionals with relevant expertise (Clinical trialists, statisticians, surgeons and geriatricians).
Review by Research & Development department at NHS Greater Glasgow & Clyde (Sponsor Institution).Review by North West Surgical Trials Centre Trial Adoption Committee.

### Validation

Data validation will be performed by local teams on 25% of data fields for 10% of cases. The validated fields will include key demographic and outcome data.

### Data management

Completed datasets will be entered into an established and specifically designed online secure electronic database (REDCap, www.project-redcap.org). Password-protected login details will be provided to local collaborators permitting secure data entry into the database. All data will be handled in accordance with the Data Protection Act 1998. All transmission and storage of data will be encrypted and compliant with HIPAA security guidelines.

No patient identifiable information will be uploaded or stored on the secure database. Collaborators will anonymise patients by recording patient hospital numbers alongside database numbers in a separate spreadsheet in order to aid the collection of data locally.

### Statistical analysis and power calculation

Using OPSOC data, frailty exists in 28% of older patients admitted with emergency surgical conditions. Fifty-four per cent of the frail people who underwent surgery had died after 90 days. In order to detect a 10% difference in mortality rate at day 90 between frail and non-frail patients, a sample size of 480 is required, given an expected mortality proportion in those not frail of 0.075 and those frail of 0.175 (data from OPSOC), assuming an 80% power. We anticipate minimal patients who are lost to follow-up and to account for this, we will aim to recruit 500 patients.

Statistical support will be provided by OPSOC. Data will be analysed for correlation between frailty and postoperative outcomes, including 90-day mortality, complications and loss of independence.

Our primary analysis will be a logistic regression of 90-day mortality by frailty, adjusted for age (65–74, and >75 years old) and gender. We will carry out a secondary analysis of the primary outcome by including additional clinical mediators which are determined statistically important using a likelihood ratio test with a stepwise model fitting approach of nested regression models, and presented as a final multivariable model. All analyses will be presented as adjusted OR with associated 95% CIs and p values.

All other outcomes will be analysed as per the above analysis, but will be deemed secondary outcomes.

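### The power statement gives two unreconciled 90-day mortality figures for frail patients (54% and 17.5%), and the sample size does not use the one labelled for operated patients

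*Protocol article*

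**What the plan says.** The Protocol article, section *Statistical analysis and power calculation*, draws three figures from OPSOC data:

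- Prevalence: "frailty exists in 28% of older patients admitted with emergency surgical conditions".
- Mortality in operated frail patients: "Fifty-four per cent of the frail people who underwent surgery had died after 90 days".
- Mortality used for the sample size: "given an expected mortality proportion in those not frail of 0.075 and those frail of 0.175 (data from OPSOC), assuming an 80% power". This leads to 480 patients, raised to 500 for loss to follow-up.

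The target is worded as an absolute difference: "In order to detect a 10% difference in mortality rate at day 90 between frail and non-frail patients". The abstract repeats the claim without qualification: "This study has been powered to detect a 10% change in mortality associated with frailty (n=500 patients".

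The *Inclusion criteria* admit only patients who undergo a non-elective abdominal procedure on the GI tract, so everyone in the study has been operated on.

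**The concern.** The 54% and the 17.5% share a source, a time point and the label frail, yet they differ about threefold (0.54/0.175 = 3.1). Nothing in the text says how they relate. By its wording, the 54% describes the group closest to the frail patients who will be enrolled, and the calculation does not use it. The 17.5% carries no stated population, and the 28% that sets the group split is expressly for admissions.

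This is the only justification given for the sample size on the primary outcome. For a fixed absolute difference, the variance of a comparison near 50% mortality is about twice that at the rates used. If 54% is right, a reader of a null result would credit the study with 80% power against a 10-point difference when it had much less.

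**Working it through.** **Inputs from the document.** Mortality 0.075 (non-frail) and 0.175 (frail); 0.54 in operated frail patients; 28% frail; 80% power; N = 480, recruiting 500.

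**Assumption.** Alpha is not stated. Two-sided 0.05 is assumed, in line with the planned 95% confidence intervals, so (1.960 + 0.842)² = 7.849. All calculations are unadjusted, whereas the primary analysis adjusts for age and gender.

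**1. Reproduce 480.** With unpooled variance and frail share f,

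N = 7.849 × [p0(1−p0)/(1−f) + p1(1−p1)/f] / (p1−p0)²

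= 7.849 × [0.075×0.925/0.72 + 0.175×0.825/0.28] / 0.10²

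= 7.849 × (0.0964 + 0.5156) / 0.01 = 480.3.

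This matches the stated figure. The same formula gives 336 at a 50:50 split, 526 at 25% frail and 635 at 20% frail. At 28% frail, other standard formulas give 395 (pooled), 444 (pooled with continuity correction), 394 (logistic regression) and 409 (arcsine). A pooled formula at 20% frail would also come close (79.9% power at 480), but 20% is not in the document. With the document's own inputs, the 28% quoted for admissions is what yields 480.

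**2. Keep the 10-point difference and put frail mortality at 0.54.** Non-frail mortality is then 0.54 − 0.10 = 0.44. This is derived; the document gives no rate expressly for operated non-frail patients.

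- Sample size for 80% power: 7.849 × [0.44×0.56/0.72 + 0.54×0.46/0.28] / 0.01 = 7.849 × (0.3422 + 0.8871) / 0.01 = 965. The ratio to step 1 is 965/480 = 2.0.
- Power at N = 500 (360 non-frail, 140 frail): SE = √(0.2464/360 + 0.2484/140) = 0.0496; 0.10/0.0496 − 1.960 = 0.057; power = Φ(0.057) = 52%.
- Smallest difference below 54% with 80% power at N = 500, solving d = 2.802 × SE: 13.8 points at 28% frail (about 40% against 54%), and about 15.5 points if 20% are frail (illustrative).

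**3. Keep 0.54 but carry the planned association through in other ways** (N = 500, 28% frail).

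- Planned odds ratio: (0.175/0.825)/(0.075/0.925) = 0.2121/0.0811 = 2.62. Odds at 0.54 are 1.174; 1.174/2.62 = 0.449, so non-frail mortality is about 31%. Power exceeds 99% (about 98.7% if 20% are frail).
- Planned risk ratio: 0.54 × 0.075/0.175 = 0.23. Power exceeds 99%.
- Stated non-frail rate of 0.075. Power exceeds 99%.

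For comparison, 0.44 against 0.54 is an odds ratio of (0.54/0.46)/(0.44/0.56) = 1.49, a much weaker association than the planned 2.62.

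**4. If 0.175 is the operated rate** and 28% holds for operated patients, step 1 applies and the stated 80% stands.

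**The case against.** The strongest reply is that the two figures need not conflict. The 54% is labelled for people who had surgery, and the 17.5% could cover all frail admissions, operated or not. That stands: the figures are unreconciled, not shown to be incompatible. It does not remove the problem, because on that reading the calculation describes a population the study does not enrol.

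A second reply is that the 52% rests on a non-frail rate of 44% that the document never gives, and on the absolute gap staying at 10 points while frail mortality triples. The primary analysis is a logistic regression, with results presented so: "All analyses will be presented as adjusted OR with associated 95% CIs and p values". On the odds-ratio scale, the planned effect carried to 54% leaves power above 99%. This also stands. The fixed 10-point case is still relevant because the text and the abstract word the target that way, but of the four ways of carrying 54% through it is the only one that loses power.

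A reader might therefore infer that the study is underpowered, or that the 80% claim has been shown to be false. The document supports neither. The loss is conditional on 54% being right and on a true difference of about 10 points, and the 54% may itself be the slip.

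**Conclusion.** The concern holds as a problem of input consistency, not as an arithmetic error. One section attributes two frail mortality figures to one source, leaves them unreconciled, and bases the sample size on the one not labelled for operated patients, together with a prevalence labelled for admissions.

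The size of the problem depends on which figure is right. If 54% is the operated rate, 80% power for a 10-point absolute difference does not hold; under the assumptions in step 2 it is about 52% at 500 patients. If 17.5% is the operated rate, with 28% frail among operated patients, the 80% stands. Power for the effect that actually exists cannot be judged from the document, because operated non-frail mortality and operated frailty prevalence are not given.

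**What to change.** From the OPSOC operated subset, state the frailty prevalence and the 90-day mortality in frail and in non-frail patients. Say which population each figure now quoted describes. Then restate, in the power section and in the abstract, the power and the detectable difference at n = 500, both as an absolute difference and as an odds ratio, with alpha given. If 54% is an error, remove it and say that 7.5% and 17.5% refer to operated patients.

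The 14-point and 52% figures should not be inserted as they stand. They use the 28% prevalence that is itself in question and a derived non-frail rate, so they must wait until the operated-patient inputs are confirmed.

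The cost is a re-tabulation of data OPSOC already holds and a change of wording. No extra patients and no change to data collection are needed. The drawback is that the stated figure may become less favourable.

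### The primary model adjusts for age in two bands that omit age 75 and leave age differences above 75 unadjusted, so the frailty odds ratio may be inflated

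*Protocol article*

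**What the plan says.** The section on statistical analysis and power calculation in the Protocol article defines the primary analysis as a logistic regression of 90-day mortality on frailty, "adjusted for age (65–74, and >75 years old) and gender". Age and gender are the only covariates in that model. The inclusion criteria set the age range as "Patients aged ≥65 years", with no upper limit.

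A secondary analysis of the primary outcome adds clinical mediators chosen stepwise; no finer age term is named. All other outcomes are to be analysed in the same way, so the age coding carries over to them. Nothing elsewhere in the article assigns age 75 to a band.

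Frailty is measured on the Clinical Frailty Score: "The score ranks from 1 to 7 with a score of ≥5 being classed as frail". The planning figures are that "frailty exists in 28% of older patients admitted with emergency surgical conditions" and an "expected mortality proportion in those not frail of 0.075 and those frail of 0.175", "assuming an 80% power".

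**The concern.** There are two separate problems.

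- **The gap.** The bands 65–74 and >75 leave out age 75. Followed literally, the model has no age value for those patients. If the boundary is settled only at analysis, someone has to choose it after the outcomes are known.
- **The coarseness.** A single upper-band indicator removes the contrast between the two bands and nothing within them. The upper band runs from the mid-seventies to the oldest patients. If older patients in that band are more often frail and also more likely to die, part of the age effect is credited to frailty.

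The protocol states this coding outright, so it is not a detail left to an analysis plan. The background section says the results should support surgical decisions and consent discussions, so an inflated odds ratio would have practical consequences.

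**Working it through.** **1. Planning figure.** Inputs from the power calculation: p1 = 0.075 (non-frail), p2 = 0.175 (frail), 28% frail, 80% power. Alpha is not stated; two-sided 0.05 is assumed. With k = 0.28/0.72 = 0.3889 and unpooled variances:

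n(non-frail) = (1.960 + 0.842)² × [0.075×0.925 + (0.175×0.825)/k] / 0.10² = 345.8

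Total = 345.8 × 1.3889 = 480.3, which reproduces the stated 480. The calculation has no age term, so the age bands do not affect it.

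**2. Planned effect and its precision.** Odds ratio = (0.175/0.825)/(0.075/0.925) = 2.62. With 500 patients there are 140 frail (24.5 expected deaths) and 360 non-frail (27 expected deaths), so overall mortality is 51.5/500 = 10.3%.

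SE(log OR) = √(1/24.5 + 1/115.5 + 1/27 + 1/333) = 0.30, giving a 95% CI of about 1.46 to 4.7.

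**3. Patients aged exactly 75.** The documents give no age distribution. Across the assumed ones (flat to 75 then declining 4% or 8% per year, and gamma shapes starting at 65) the share is about 4–6%, or 19–32 of 500. The allowance for losses is 500 − 480 = 20.

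**4. Residual confounding with no true frailty effect.** Assumed: gamma-shaped ages from 65 with mean about 75, 28% frail, 10.3% mortality, frailty and death both logistic in age. The share left is ln(two-band OR)/ln(unadjusted OR).

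| OR per decade, frailty / death | Unadjusted OR | Two-band OR | Share left |
|---|---|---|---|
| 1.65 / 1.5 | 1.12 | 1.05 | 0.049/0.113 = 43% |
| 2.2 / 1.8 | 1.30 | 1.13 | 0.122/0.262 = 47% |
| 2.7 / 2.2 | 1.53 | 1.23 | 0.207/0.425 = 49% |

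Varying the gamma shape with the same gradients widens the two-band OR to 1.03–1.24 and the share left to 38–48%.

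**5. Residual confounding with a true OR of 2.62.** Assumed: ages 65–99, flat to 75 then declining as in step 3. Gradients are per year of age. Selected rows:

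| Decline per year | OR per year, frailty / death | Unadjusted | Two bands (75 in upper) | Two bands (75 dropped) | Five-year bands | Linear age |
|---|---|---|---|---|---|---|
| 8% | 1.05 / 1.03 | 2.91 | 2.73 | 2.72 | 2.63 | 2.62 |
| 8% | 1.08 / 1.05 | 3.42 | 2.95 | 2.92 | 2.64 | 2.62 |
| 4% | 1.12 / 1.08 | 4.97 | 3.66 | 3.57 | 2.70 | 2.62 |

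Over the full grid the two-band OR is 2.73–3.66, and 41–52% of the total age confounding is left. Of that residual, 91–98% arises in the upper band. Dropping the 75-year-olds barely moves the estimate. With no association between age and frailty, the two-band OR is 2.53–2.61, so there is no inflation.

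**6. Bias against sampling error.** Null case: ln(1.03)/0.30 = 0.1 SE to ln(1.24)/0.30 = 0.7 SE. Steepest row in step 5: ln(3.66/2.62)/0.30 = 1.1 SE.

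**The case against.** Several points on the other side stand.

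- **The gap at 75 is probably typographical.** Nothing suggests that 75-year-olds are to be excluded. A reader might infer that they will be lost from the model; that is the literal reading, not the likely outcome.
- **The size of the bias is assumed.** The documents give no age gradient for frailty or mortality, and the cohort is restricted to patients selected for surgery, in whom the age–frailty gradient is unknown. A reader might infer that the odds ratio is certainly biased upward; the documents support that only if both rise with age above 75.
- **About half of the confounding is removed.** A reader might infer that most of the age confounding remains. Among patients above 75, the band indicator does remove none of it. From 65 upward, the two bands remove roughly half.
- **The benchmark is favourable by construction.** The data were generated as linear in age on the logit scale, so a linear term recovers the truth exactly. This does not show that it would do so in the real cohort, which is one reason to allow a spline.
- **Precision and purpose.** The illustrated bias is mostly below one standard error, and the stated aim is correlation, for which leftover age matters less than for a causal claim. This lowers the severity but does not remove the point: the plan chose to adjust for age, and bias of this kind does not shrink with more patients.

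**Conclusion.** The point holds as a should-fix. It is certain from the text that age 75 is unassigned and that one open-ended band leaves age differences above 75 unadjusted. Inflation of the frailty odds ratio is conditional on frailty and 90-day mortality both rising with age in that range. Under the assumed gradients, roughly 40–50% of total age confounding is left, with an illustrative frailty odds ratio of about 1.03–1.24 when the truth is 1. The gap at 75 itself has little effect on the estimate.

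The documents do not support a conclusion that the primary analysis is invalid. Even the largest null-case figure, 1.24, is far from the planned odds ratio of 2.62, and the sample size is unaffected.

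**What to change.** In the primary analysis sentence, replace the two bands with age in years, either linear or as a restricted cubic spline with 3 knots. State that the same term is used in the secondary-outcome models, which follow the primary one. Write any bands kept for tables as 65–74 and ≥75, and settle this before outcomes are seen.

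This assumes that exact age or date of birth is captured among the basic demographics. The case report form is in a supplementary appendix that is not shown, so this is an inference, although screening on age makes it likely. If only grouped age is held, use narrower bands that cover every age; five-year bands gave 2.63–2.70 against a true 2.62 in the illustration.

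The cost is a one-sentence edit. A linear term uses the same single degree of freedom as the two bands, and a 3-knot spline uses one more. The target of 500 does not change.
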